18^, therefore, further studies are necessary to verify the benefit of tCDS in association with other therapies. For that reason, the primary objective of this study is to assess whether tDCS can enhance and prolong the effects of videogame training on improving postural balance in the older people. Secondarily, check if there is a relationship between the response to training and the quality of life. This study hypothesizes that the association of tDCS with virtual reality therapy is more effective in improving balance in the older people than therapy with videogames alone, and that the addition of tDCS will prolong the effects of balance training.

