### Recruitment and allocation

Participants in this study will be community elders elected according to the criteria established for allocation. They will be randomized into 3 groups:

Group 1: Control Group (Video game balance training);

Group 2: Anodal group (Video game balance training associated with anodal tDCS);

Group 3: Sham Group (Video game balance training associated with sham tDCS).

A researcher not involved in evaluations or training will be responsible for allocating participants via
www.randomization.com.

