### Sample size

The sample size was obtained using
G*Power 3.0.10 software, based on the outcomes from a pilot study. The calculation was carried out by the two-way repeated measures analysis of variance (ANOVA), considering the mean value (before and after training, and 30-day follow-up) for the control groups (25.46) active (27.46) and sham (24.66) and the pooled standard deviation (SD
_pooled_) (2.89), with α = 0.05, β = 0.2 (80% of power) and the effect size of 0.40. A total of 15 individuals were determined to be required for each group (total sample: 45 individuals). Considering possible dropouts and to ensure a sample size that will demonstrate the effect of the intervention, the sample will be expanded by 25%, resulting in 19 individuals in each group, thus totalling 54 participants.

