### Outcome assessments

All evaluations will be carried out on three occasions: pre-intervention, after eight treatment sessions and 30 days after the end of the training (follow-up). The training will be held twice a week, for 4 weeks, totalling 8 sessions.

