### Primary outcomes

***Postural balance***. The assessment of postural balance will be performed by the Mini BESTest Scale, which consists of 14 functional tasks, such as sitting and getting up from a chair, standing up, balancing on tiptoes, and on one foot, overcoming walking obstacles, and double activities task
^21^.

Performance can range from 0 to 28 points. Each test can be performed for up to three attempts and the best result will be obtained. If adaptations are necessary to accomplish this, a point will be deducted from the maximum score obtained. This is a very reliable instrument, with an intraclass correlation (ICC) of 0.84)
^22^.

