### Statistical analysis

All statistical tests will be performed using
SPSS (V22, IBM Corporation, New York, USA). Initially, we will perform the test of normality of the sample using the Shapiro-Wilk test, considering the significance level defined as a value of α < 0.05. The parametric data will be expressed as a mean ± SD (standard deviation), and the nonparametric data as a median (IQR); the categorical data will be described as absolute values and as a percentage of the total sample.

The variables of the data of the Mini-BESTest, Posturography, obtained pre-intervention, post-intervention and 30-day follow-up for the three groups (control, active and sham) will be calculated by the two-way repeated measures analysis of variance (ANOVA) for the parametric data and the Friedman’s test for the nonparametric data.

Finally, to verify whether there is a correlation between BESTest values and the symptoms of depression and quality of life, Pearson’s R correlation (parametric) or Spearman correlation (nonparametric) for the three groups in three evaluated times will be performed, verifying the degree of correlation (r) and its significance (p).

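### Friedman's test, the planned fallback for non-normal balance data, has no group term, so on that branch the tDCS hypothesis has no valid planned test

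*Protocol article*

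**What the plan says.** The hypothesis in the Introduction compares groups: "the association of tDCS with virtual reality therapy is more effective in improving balance in the older people than therapy with videogames alone". It adds that tDCS will make the benefit last longer. Under Recruitment and allocation, participants are allocated to control, anodal or sham ("They will be randomized into 3 groups"). They are assessed three times: before training, after eight sessions and 30 days after training ends.

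The Statistical analysis section opens with a gate: "Initially, we will perform the test of normality of the sample using the Shapiro-Wilk test", at the 0.05 level. It then assigns Mini-BESTest and posturography, for three groups at three times, to "two-way repeated measures analysis of variance (ANOVA) for the parametric data and the Friedman’s test for the nonparametric data".

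The only other rank method in the article is Spearman's correlation, used for depression symptoms and quality of life. No rank test that compares groups is named.

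On the primary outcome, the Primary outcomes section says: "Performance can range from 0 to 28 points". The Eligibility criteria admit people scoring 25 or below.

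**The concern.** The two tests are offered as alternatives for the same question, but they answer different ones. A two-way repeated measures ANOVA has terms for group, time and group by time, and the tDCS hypothesis lies in the group and interaction terms. Friedman's test is the rank counterpart of a one-way repeated measures analysis and covers time only.

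If the data are judged non-normal, the planned p-value for the primary outcome would say whether scores changed across visits. All three arms receive game training, so such a change is expected even if tDCS adds nothing. The analyst would then have no planned group comparison. The remaining options would be to choose one after seeing the data, or to run Friedman in each arm and compare which arms reach significance. The latter is not a valid comparison of groups.

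**Working it through.** **1. What the trial was sized to test.** Inputs from the Sample size section: means 25.46 (control), 27.46 (active) and 24.66 (sham), SD 2.89, α 0.05, power 80%, effect size 0.40, 15 per group.
- Grand mean = (25.46 + 27.46 + 24.66)/3 = 25.86. Deviations are −0.40, 1.60 and −1.20.
- f = √[(0.16 + 2.56 + 1.44)/3]/2.89 = 1.178/2.89 = 0.407, which matches the stated 0.40.
- For the between-group effect with m = 3 visits, λ = f²·N·m/[1 + (m − 1)ρ]. The article gives no correlation. Assuming ρ = 0.5 and N = 45, λ = 0.16 × 45 × 3/2 = 10.8 on 2 and 42 degrees of freedom, and power is 81.7%. N = 45 is the smallest equal-group total reaching 80%, so the stated figure is reproduced. With ρ from 0.3 to 0.8 the total runs from 36 to 57.
- At ρ = 0.5 the interaction test would need 18 in total and a one-way ANOVA 66. The stated 45 therefore fits the between-group test, which the Friedman branch lacks.

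**2. What Friedman's test uses.** With n participants, k visits and rank sums R_j, Q = [12/(nk(k + 1))]·ΣR_j² − 3n(k + 1). For n = 45 and k = 3 this is ΣR_j²/45 − 540. Ranks are taken within a person, so adding a constant to all of one person's scores changes nothing, and group does not appear. On one simulated data set Q was 16.84. It stayed 16.84 after adding 10 points to every active-arm score (a purely mathematical check, since real scores stop at 28) and again after shuffling group labels.

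**3. How the tests behave.** Simulation with 15 per arm, SD 2.89, ρ = 0.5, normal scores and 3,000 runs; ρ, the 22-point baseline in the last two rows and the gains are assumptions. Entries are the share of runs with p < 0.05.

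| Scenario | Pooled Friedman | ANOVA group term | Kruskal-Wallis on pre-to-post change |
|---|---|---|---|
| Planning means held at all three visits | 5% | 84% | 5% |
| Every arm gains 2, no tDCS effect | 99% | 5% | 5% |
| Control +2, active +4, sham +2 | 100% | 33% | 43% |

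The first row has constant group differences and no change over time, so Kruskal-Wallis on change has nothing to detect there. Between the last two rows pooled Friedman is near 100% whether or not tDCS works. Kruskal-Wallis on change separates the two cases.

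Run arm by arm with equal 2-point gains, Friedman gave differing verdicts across arms in 71% of runs. In a second set-up (ρ = 0.6, rounded scores, entry cut and cap applied) the figure was 24% for a 2-point gain and 1% for a 3-point gain. The rate depends on the assumptions; the comparison is invalid at any rate.

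**4. How likely the fallback is.** The article does not say whether Shapiro-Wilk is run per group and visit, per visit or on all data, nor how many rejections trigger the switch. The assumed set-up is SD 2.89, ρ = 0.6, rounded scores, entry at 25 or below, cap at 28 and 15 per arm.

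| Reading of the rule | Latent baseline mean 20, gain 2 | Latent baseline mean 23, gain 2 | Latent baseline mean 23, gain 3 |
|---|---|---|---|
| One test on all post-training scores | 12% | 68% | 99% |
| Any of nine group-by-visit tests | 49–53% | 83–85% | 96–97% |

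Across 2- and 3-point gains, single group-by-visit tests reject in about 8% to 34% of cases.

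**The case against.** The strongest reply is that the defect is conditional. The ANOVA is named for parametric data, contains the group and interaction terms, and is the test the sample size was built on. That stands. A reader might infer that the trial has no valid group test at all; the document does not support this.

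A reader might also infer that the fallback is nearly certain. The high rates need an any-of-nine rule the article does not state, or a baseline close to the entry limit. The planning mean of 27.46 does not settle it. A normal curve with that mean and SD 2.89 puts 43% of scores above 28, but the Sample size section appears to give it as a mean over all three visits. With entry at 25 or below and a cap of 28, such a mean cannot exceed (25 + 28 + 28)/3 = 27.0, so it is no sound basis for a trigger rate.

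The 99% and 100% rejection rates for Friedman could be mistaken for false-positive rates. They are correct detections of change over time. Nor does the article say that significance will be compared arm by arm. That is a risk the plan leaves open, not something it states.

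Finally, a separate analysis plan might add a group comparison. Leaving detail to such a plan would be no fault. Here, however, the article itself names the wrong test as the substitute, and an analysis plan would have to contradict it.

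**Conclusion.** The point holds, and it is confined to the non-parametric branch for Mini-BESTest and posturography. There, Friedman's test cannot address the between-group hypothesis, and no other rank-based group comparison is planned. This conclusion follows from the form of the test and rests on no simulated figure.

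The chance of reaching that branch does rest on assumptions. It runs from about 12% (one test on all post-training scores, baseline 20, 2-point gain) to over 95% (baseline 23, 3-point gain). A bounded integer score with a restricted entry range makes the fallback a realistic event, but no single probability can be given. The ANOVA branch is sound on this point, and nothing here requires replacing it with another model.

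**What to change.** Replace Friedman's test as the fallback with a rank-based method that compares groups. Options are Kruskal-Wallis on change from baseline at each of the two later visits, rank-ANCOVA with the baseline score as covariate, or a group-by-time rank test.

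Preferably, keep the group-by-time model as the primary analysis whatever Shapiro-Wilk shows, check its residuals, and report the chosen rank method as a sensitivity analysis. This removes the data-driven switch. If the switch is kept, state which data the normality test is applied to and what result triggers it. Moving to a baseline-adjusted mixed model would be an optional improvement and is not needed to cure this defect.

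The cost is wording in the Statistical analysis section. Because the Trial status section says data collection is already under way, the change should be documented and dated before any unblinded analysis. Kruskal-Wallis on change and rank-ANCOVA need no new data or software. If a group-by-time rank test is preferred, first confirm that it can be run in the named SPSS version.

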### Potential confusion factors

***Symptoms of depression***. The symptoms of depression will be evaluated and classified according to severity, using the Beck Depression Inventory (BDI), a questionnaire composed of 21 questions, which can be self-applied. Scores from 0 to 10 indicate an absence of depression; 11 to 18 indicate mild depression; 19 to 29 indicate moderate depression and 30 to 63 is considered severe depression
^25^. In studies with the older people, the BDI score shows a degree of reliability r = 0.78
^26^. Subsequently, it will be assessed whether the emotional state interfered with the results.

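### The planned correlations relate balance scores, not response to training, to quality of life, and quality of life is left out of the stated group comparison

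*Protocol article*

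**What the plan says.** The Introduction of the protocol article gives one objective that involves quality of life: "Secondarily, check if there is a relationship between the response to training and the quality of life".

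Under Outcome assessments, all evaluations are made before training, after the eight sessions and 30 days later. Quality of life (WHO instrument, brief version, scored as a total of 26 to 130) is listed under Secondary outcome. The Beck Depression Inventory (BDI) is listed under Potential confusion factors, with the promise: "Subsequently, it will be assessed whether the emotional state interfered with the results".

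Statistical analysis has two analytic steps. The group comparison, by two-way repeated-measures ANOVA or Friedman's test, covers "The variables of the data of the Mini-BESTest, Posturography, obtained pre-intervention, post-intervention and 30-day follow-up for the three groups". Neither quality of life nor BDI is named there. Both enter only in the last step, which is meant "to verify whether there is a correlation between BESTest values and the symptoms of depression and quality of life", using Pearson or Spearman coefficients with p-values, "for the three groups in three evaluated times will be performed".

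**The concern.** A response to training is a change from before to after. The planned correlations use the Mini-BESTest score as it stands at each visit, including the visit at which nobody has yet trained and no response can exist. No change score or baseline-adjusted score is defined. Followed as written, the analysis would report whether people with better balance also report better quality of life. That is a different question from whether people who improved more differ in quality of life.

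Two related gaps sit in the same section. Quality of life is a secondary outcome measured three times in a randomised trial, yet the stated group comparison would give no between-arm result for it. And a correlation between BDI and balance, by itself, does not show whether emotional state interfered with the comparison of arms. BDI measured after randomisation may also have been affected by the treatment.

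**Working it through.** **1. Objective against analysis.** The article states no figure for the correlations, so there is none to reproduce. The check is whether the planned coefficients determine the quantity in the objective.

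Let B be Mini-BESTest and Q quality of life. Assume, for illustration, equal SDs at both visits, a same-visit correlation r = 0.5 at both visits, and a visit-to-visit correlation of 0.7 for each scale. Let c be the cross-visit correlation (B at one visit with Q at the other). None of these values is in the article.

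- If change in quality of life is meant: corr(ΔB, ΔQ) = (2r - 2c) / (2 - 2 × 0.7) = (1 - 2c) / 0.6.
  - c = 0.35: 0.30 / 0.6 = +0.50
  - c = 0.50: 0 / 0.6 = 0.00
  - c = 0.60: -0.20 / 0.6 = -0.33
- If baseline quality of life is meant: corr(ΔB, Q_pre) = (c - r) / √(2 - 2 × 0.7) = (c - 0.5) / 0.775.
  - c = 0.35: -0.19
  - c = 0.50: 0.00
  - c = 0.60: +0.13

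Under either reading the answer turns on c, a cross-visit correlation that the plan never computes. The same-visit coefficients are 0.5 in every row, yet the sign of the response relationship differs.

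A simulated case agrees. Take Q fixed over time, B_pre correlated 0.50 with Q, and a change in B (SD 0.7) unrelated to Q. The post-training correlation is 0.5 / √(1 + 0.49) = 0.41, so both visits show a clear association while the correlation of Q with change is 0.00.

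**2. Pooled or per arm.** The wording on groups and times does not say that coefficients are computed separately in each arm. Pooling over arms would still correlate levels, so step 1 holds either way.

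**3. Number of tests, if run per arm and visit.** 2 variables (BDI, quality of life) × 3 groups × 3 times = 18. With all nulls true and independent tests at 0.05, the chance of at least one p < 0.05 is 1 - 0.95^18 = 0.60. The same people are measured repeatedly on the same scales, so the tests are correlated and 0.60 is an upper-end illustration.

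**4. Detectable correlation per test.** Sample size gives 15 per group before the dropout allowance and 19 after it. (The total of 54 implies 18 per group, since 19 × 3 = 57; that is a separate matter and lies inside the range.) By Fisher's z, two-sided 0.05 and 80% power, |r| = tanh[(1.96 + 0.84) / √(n - 3)].

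| n | √(n - 3) | |r| for 80% power |
|---|---|---|
| 15 | 3.46 | 0.67 |
| 19 | 4.00 | 0.61 (0.605) |
| 45 (all arms) | 6.48 | 0.41 |
| 54 (all arms) | 7.14 | 0.37 |

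**5. Group comparison.** The list of variables for the ANOVA or Friedman test names Mini-BESTest and posturography. Set beside the Secondary outcome section, quality of life is the one declared outcome left out. No BDI term appears in that comparison.

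**The case against.** The article is a condensed protocol, and an unseen analysis plan may define response and add covariates. That would answer an omission. Here the article states an analysis, and that analysis does not fit the objective in its own Introduction, so the stated text needs correcting.

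Several stronger readings are tempting and are not supported:

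- A reader might infer that the BDI correlation is the promised check on emotional state, so that the plan certainly leaves that question unanswered. Statistical analysis never says so, and Potential confusion factors gives no method. What stands is narrower: the correlation alone would not answer the question, and no other method is described here.
- A reader might take the 18 tests and the 60% as facts of the plan and conclude that a spurious finding is likely. Both depend on the per-arm, per-visit reading, and the 60% also on independence.
- A reader might count four quality-of-life domains plus BDI, giving 5 × 3 × 3 = 45 tests and 1 - 0.95^45 = 0.90. The article quotes reliabilities by domain, but it defines the score as a single total and the analysis says only quality of life. The plan does not specify 45 tests.
- A reader might say that the missing arm comparison for quality of life fails a stated objective. It does not, because the only quality-of-life objective is a relationship. The gap is that a declared secondary outcome receives no group comparison.

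It is also fair that low power and unadjusted p-values are weak complaints against secondary correlations for which the article claims no power. Those figures are therefore not the main argument.

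**Conclusion.** The mismatch holds. As written, the plan cannot answer its secondary objective, because correlations of score levels leave the relationship with response undetermined even in sign. This rests on the wording of the article and on algebra. The values 0.5, 0.7 and the range for c are illustrative, and other values would change the numbers but not the conclusion. It does not depend on whether arms are pooled.

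The absence of quality of life from the stated group comparison also holds, as a gap in the analysis of a declared outcome. On depression, the supportable statement is only that the described correlation is insufficient for the question raised.

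The multiplicity and power figures are secondary and conditional on the stratified reading. The randomised comparison of the primary outcome is unaffected. The change should be made, but it does not threaten the trial's main result.

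**What to change.** Amend Statistical analysis as follows.

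- **(a) Response and quality of life.** Define response as the pre-to-post change in Mini-BESTest. Replace the level correlations with one model over all participants relating that change to quality of life, adjusted for arm and baseline Mini-BESTest. State whether baseline quality of life or its change is meant, since the Introduction allows either; if change, adjust for baseline quality of life as well. With 45 to 54 participants, one such analysis would detect |r| of about 0.41 to 0.37 with 80% power, ignoring the few degrees of freedom spent on covariates.
- **(b) Quality of life by arm.** Add quality of life to the same group-by-time comparison as Mini-BESTest and posturography.
- **(c) Depression.** As a sensitivity analysis, add baseline BDI to the Mini-BESTest model, with a BDI-by-arm term labelled exploratory. The main effect alone adjusts the arm comparison but does not test whether depression altered the arm effect. Do not use BDI measured after randomisation.

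The cost is analysis wording only. All three instruments are already scheduled at the visits needed, so no new data, visits or participants are required.

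### The links of balance with quality of life and with depression are each judged from about nine arm-by-visit p-values with no deciding test, so false-positive risk per question is roughly 24% to 37% and power in each cell is low

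*Protocol article*

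**What the plan says.** The Introduction sets the secondary objective: "Secondarily, check if there is a relationship between the response to training and the quality of life". The section on potential confusion factors adds, for the Beck Depression Inventory (BDI), "Subsequently, it will be assessed whether the emotional state interfered with the results".

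Both questions are handed to one sentence at the end of the Statistical analysis section. It plans a Pearson or Spearman "correlation between BESTest values and the symptoms of depression and quality of life", and says that this "for the three groups in three evaluated times will be performed, verifying the degree of correlation (r) and its significance (p"). The Outcome assessments section states that "All evaluations will be carried out on three occasions", so all three scales are available at every visit.

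The article does not say which correlation answers either question. The only significance level in the Statistical analysis section is in the sentence on the normality test: "considering the significance level defined as a value of α < 0.05". The sample size calculation also uses 0.05.

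**The concern.** Each question asks for one answer: is there a relationship or not? The plan supplies a grid of p-values, split by arm and by visit, with no order among them. A grid like this fails in two ways. If there is no association, one of the cells may well fall below 0.05 by chance and can be presented as the relationship. If there is a moderate association, each cell is too small to show it reliably, so the expected picture is a scatter of significant and non-significant cells. A reader could then take differences in significance between arms as a sign that stimulation changes the relationship, which such differences cannot show.

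At stake are the stated secondary objective and the check on depression. Neither objective requires splitting the sample by arm. The fault lies in the number and splitting of the tests; it would remain if changes were correlated instead of levels.

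**Working it through.** **Inputs from the article.** Three arms, three visits, two scales (depression, quality of life). 15 per arm before the dropout allowance. After it, 19 per arm is stated, but the stated total of 54 is 18 per arm. Alpha 0.05. Mini-BESTest reliability (ICC) 0.84, used only as a guide to how strongly visits may correlate.

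**Assumptions, because the article gives no figures.** The correlation between visits, the correlation between the two questionnaires, 0.05 for each correlation test, and that any one significant cell is reported as a relationship.

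**The plan's own figure.** The article gives no error rate for the correlations; its only computed figure is the sample size. Pilot means are given "for the control groups (25.46) active (27.46) and sham (24.66"), with pooled SD 2.89. Their average is 25.86 and the deviations are −0.40, 1.60 and −1.20. So f = √[(0.16 + 2.56 + 1.44)/3] / 2.89 = 1.178/2.89 = 0.407, in line with "β = 0.2 (80% of power) and the effect size of 0.40". For the between-groups factor with 3 measurements, f = 0.40 and an assumed correlation of 0.5, N = 45 gives power 0.817. The 15 per group is reproduced. It was sized for the balance comparison, not for correlations within an arm.

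**Number of tests.** 3 arms × 3 visits = 9 per scale; × 2 scales = 18, if quality of life is one total score. If its four domains were tested separately, (4 + 1) × 9 = 45.

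**Chance of at least one p < 0.05 with no association, independent tests** (1 − 0.95^k):
- nine tests (one question): 1 − 0.95^9 = 0.370
- 18 tests (both questions): 1 − 0.95^18 = 0.603
- arms pooled, three visits (one question): 1 − 0.95^3 = 0.143
- arms pooled, both questions: 1 − 0.95^6 = 0.265

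**Allowing for dependence.** Simulation with 15, 18 or 19 per arm, Pearson tests, balance unrelated to either scale, and a correlation between the two questionnaires of 0 to 0.5 in size:

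| Between-visit correlation | One question (9 tests) | Both questions (18 tests) |
|---|---|---|
| 0 to 0.84 | about 30% to 37% | about 49% to 60% |
| 0.9 to 0.95 | about 24% to 28% | about 40% to 48% |

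Simulation error is about one percentage point. A stronger correlation between the questionnaires lowers the two-question figures by a few points more. Each single test keeps its 5% level.

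**Power.** The smallest significant |r| is 0.514 at n = 15, 0.468 at n = 18 and 0.456 at n = 19. Fisher's z for r = 0.3 is 0.3095.
- One cell of 15: 0.3095 × √12 = 1.072; power about 19%. A cell of 19: 0.3095 × √16 = 1.238; power about 24%.
- All 45 together, adjusted for group (two degrees of freedom lost): 0.3095 × √40 = 1.957; power about 50% at 0.05, or about 39% at Holm's first step (0.025).

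**The case against.** Several points against this are fair.

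- **The split by arm is a reading.** The preceding paragraph uses a similar phrase about the three groups for a single ANOVA across all arms. The sentence could mean correlations over all participants at each visit: six tests, not 18. The arm-by-visit reading is the more natural one, but 18 is not a guaranteed minimum.
- **The 0.05 level is inferred** from the normality-test sentence and the sample size.
- **The article has no rule that one significant cell settles the question.** It says only that r and p will be reported. It also plans no comparison of correlations between arms, so a misreading of that kind is a risk in the later report, not part of the plan.
- **Multiplicity control for secondary correlations is often left to an analysis plan**, which is not shown. This weakens a complaint that control is missing. It does not meet the point that the article itself fixes an unranked set of significance tests.

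A reader might infer that about half or more of trials with no relationship would report one. The documents do not support that as a flat statement. It merges two separate questions, needs the arm-by-visit reading and the any-cell rule, and fails when scores are very stable between visits. A reader might also infer that the trial's main result is compromised. It is not: these are secondary correlations, and the balance comparison between groups does not depend on them.

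**Conclusion.** The point holds in a conditional form. On the natural reading, each question is answered by nine p-values with no deciding test. If each is at 0.05 and any significant cell is reported, the false-positive chance per question is about 30% to 37% for between-visit correlations up to 0.84, and about 24% to 28% at 0.9 to 0.95. Pooling arms at each visit would bring it to about 14%, assuming independence. The per-question figure is the fairer summary, because quality of life and depression serve different purposes in the article.

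The weakness in power needs only the split by arm and the 0.05 level: about 19% for r = 0.3 in a cell of 15, and still only about 24% with 19. This should be changed, but it bears on the secondary objective and the check on depression only.

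**What to change.** Name one analysis for each question in advance, using all randomised participants together and adjusting for randomised group.

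- **Quality of life:** change in Mini-BESTest from pre- to post-intervention against one named quality-of-life score, the total score. This also matches the objective, which speaks of response to training.
- **Depression:** the same change against baseline BDI.
- **Reporting:** give each coefficient or partial correlation with a 95% confidence interval. Treat the quality-of-life test as the test of the secondary objective, or apply Holm's correction across the two.
- **Arm-by-visit correlations:** show them descriptively, without p-values. Claim a difference between arms only from a group-by-covariate interaction term.

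Power for r = 0.3 with 45 people would be about 50% at 0.05, or 39% at Holm's first step, against 19% per cell now. That is better but still modest, so the confidence interval should carry the message. The cost is a wording change and no new data. Arm-specific correlations lose their own significance statements, and the pooled estimate assumes a common slope across arms. The interaction term checks that assumption, though with limited power at this sample size.
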